##### Proxy measures of clinical practice

Secondary outcomes also include proxy measures of the clinical practices of interest. These proxy measures consist of self-report measures and clinical vignettes [64].

##### Predictors of clinical practices

Table 4 shows the factors we hypothesise to mediate the intervention effects, listed per clinical practice. Factors have been grouped into two categories: 1) collective level constructs – clinicians’ self-reported cognitions about their EDs team climate for innovation [65,66] in relation to the clinical management of mTBI in general; and 2) individual level constructs – clinicians’ self-reported cognitions in relation to each clinical practice (such as the extent to which the clinicians feel confident in screening for PTA using a validated tool (beliefs about capabilities), whether a clinician believes these clinical practices will lead to favourable outcomes (beliefs about consequences) [67], and whether a clinician intends to perform the practices) [68]. For our primary outcome, individual level predictors along the causal pathway will be assessed (see Table 4). We have decided to only include these for the primary outcome, and not other outcomes for two reasons: 1) because the primary outcome is the best measure of clinical practice from the medical records which can be measured for all patients; and 2) to reduce the responder burden for clinicians.

**Table 4 T4:** Predictors of clinical practices

	**Data collection method**	**Outcome assessment period/timing**	**Data source**	**Level data collected**	**Analysis level**
**PTA, CT, INFO**					
**Cognitions in relation to mild traumatic brain injury related team climate**					
Team climate					
• Participative safety	Staff questionnaire (4-item)	Baseline/Endpoint	Doctors	Staff member	ED
			Nurses		
• Support for innovation	Staff questionnaire (3-item)	Baseline/Endpoint	Doctors	Staff member	ED
			Nurses		
• Vision	Staff questionnaire (4-item)	Baseline/Endpoint	Doctors	Staff member	ED
			Nurses		
• Task orientation	Staff questionnaire (3-item)	Baseline/Endpoint	Doctors	Staff member	ED
			Nurses		
**Behaviourally specific cognitions**					
Intention to adhere to recommended practice					
• PTA	Staff questionnaire (1-item)	Baseline/Endpoint	Doctors	Staff member	Staff member
			Nurses		
• CT	Staff questionnaire (1-item)	Baseline/Endpoint	Doctors	Staff member	Staff member
• INFO	Staff questionnaire (1-item)	Baseline/Endpoint	Doctors	Staff member	Staff member
			Nurses		
**PTA only**					
• Knowledge	Staff questionnaire (2-item)	Baseline/Endpoint	Doctors	Staff member	Staff member
			Nurses		
• Beliefs about capabilities	Staff questionnaire (3-item)	Baseline/Endpoint	Doctors	Staff member	Staff member
			Nurses		
• Beliefs about consequences	Staff questionnaire (3-item)	Baseline/Endpoint	Doctors	Staff member	Staff member
			Nurses		
• Social influences	Staff questionnaire (2-item)	Baseline/Endpoint	Doctors	Staff member	Staff member
			Nurses		
• Environmental context and resources	Staff questionnaire (3-item)	Baseline/Endpoint	Doctors	Staff member	Staff member
			Nurses		

CT, CT scan-clinical criteria; INFO, provision of patient information; PTA, appropriate PTA screening.

Proxy measures of clinical practice and predicting factors are measured using staff questionnaires. The NET team will prepare the questionnaire packs (including invitation letters, explanatory statements and baseline questionnaires) and send these to a local survey coordinator, who will be tasked with the distribution of the packs to their randomly selected staff members (for example, via mail or pigeon hole). Non-responders will receive reminders verbally or via email, and will be sent a reminder pack [69]. Questionnaires will be available upon request, and from the website (http://www.netprogram.org.au/).

Figure 2 depicts our conceptual framework, informed by Frambach and colleagues [70], Greenhalgh and colleagues [71] and Michie and colleagues [67]. It shows the specific factors our intervention will target, listed within categories (in bold).

**Figure 2 F2:**
[figure not shown]
**Conceptual framework.** CT, CT scan-clinical criteria; HRQoL, health-related quality of life; INFO, provision of patient information; mTBI, mild traumatic brain injury; PTA, appropriate PTA screening.

##### Patient and cost outcomes

Table 5 outlines the patient and cost outcomes that will be included in the study. We hypothesise that provision of patient information containing advice, education, and reassurance upon discharge from the ED reduces anxiety and number of self-reported symptoms [40]. In addition, we will investigate whether this leads to improved post-accident functioning (return to normal activities including work and health-related quality of life (HRQoL)) and fewer adverse events (for example, re-presentations).

**Table 5 T5:** Patient and cost outcomes

	**Data collection method**	**Outcome assessment period/timing**	**Data source**	**Level data collected**	**Analysis level**
**Clinical outcomes and quality of life**					
▪ Anxiety*	CATI questionnaire (7-item)	3-5 month post-discharge	Patient	Patient	Patient
▪ Post-concussive symptoms	CATI questionnaire (13-item)	3-5 month post-discharge	Patient	Patient	Patient
▪ Return to normal activities including work	CATI questionnaire (2-item)	3-5 month post-discharge	Patient	Patient	Patient
▪ Health-related quality of life	CATI questionnaire (12-item)	3-5 month post-discharge, data collected over last month	Patient	Patient	Patient
**Healthcare utilisation and costs**					
▪ Medical and surgical services received in ED/inpatient ward (including CT scan)	Chart audit	Retrospectively on a 2 month period post-intervention	Hospital record	Patient	Patient
▪ Re-presentation to ED	CATI questionnaire (1-item)	3-5 month post-discharge	Patient	Patient	Patient
	Chart audit	Retrospectively on a 2 month period post-intervention	Patient	Patient	Patient
▪ Healthcare visits in relation to mTBI (GP, brain clinical, other)	CATI questionnaire (3-item)	3-5 month post-discharge; data collected over last month	Patient	Patient	Patient
▪ mTBI-related medication use	CATI questionnaire (4-item)	3-5 month post-discharge; data collected over last month	Patient	Patient	Patient
▪ Direct costs delivering intervention (intervention group only)	Data abstraction surveys	On completion of delivery	Admin records	Intervention components	ED

*Primary outcome. CATI, computer-assisted telephone interview; CT, computed tomography; ED, emergency department; GP, general practitioner; mTBI, mild traumatic brain injury.

Patient outcomes in the NET-Plus hospitals will be collected via a computer-assisted telephone interview by a trained researcher, following consent received via a local ED staff member. Anxiety will be measured using the relevant questions in the Hospital Anxiety and Depression Scale [72,73]. Post-concussive symptoms will be measured using the 13-item Rivermead [74]. HRQoL will be measured using a 12-item short form health survey (SF-12) and SF-12-based SF6D [75,76]. The SF6D’s six domains - physical functioning, role participation, social functioning, bodily pain, mental health, and vitality - encompass variation in patient outcomes with respect to anxiety, interference with normal work and social function due to sleep problems, and physical functioning. Australian population norms for the SF-36-based SF6D are now available [77] and the SF6D has previously been used as a measure of HRQoL in TBI [78].

### Data quality assurance

Chart auditors will be trained to identify eligible patients in the medical record system, and to log data into the secure web-based system in participating hospitals. Auditors will assess the same pilot records, and training will continue until sufficient consistency is achieved. Auditors will receive a data collection manual with instructions (such as definitions and data dictionary). The web-based database will be designed to minimise errors (for example, inability to leave particular fields open, or warning when answer is outside expected range). Double data entry will be used for all paper-based questionnaires and returned questionnaires will be checked for consistent errors or missing data.

### Sample size

The primary outcome in the NET trial is appropriate PTA screening. In the calculation of sample size for this outcome, adjustment needs to be made for the clustered nature of the design. The variance inflation factor, or design effect, used to achieve this is a function of the average cluster size, variation in cluster size, and the intra-cluster correlation (ICC) [79].

The assumed ICC was calculated from two sources reporting ICCs from various datasets [80,81]. We included only ICCs for process measures in secondary care settings since empirical research has demonstrated that ICCs tend to be larger for 1) process measures compared with patient outcomes (median 0.063 versus 0.030, respectively), and 2) secondary care compared with primary care (median 0.061 versus 0.045) [63]. Thirty three ICC estimates for process measures in secondary care were available, and the median ICC was 0.18. The variation in cluster size was incorporated into the sample size calculation through an estimate of the coefficient of variation, defined as the ratio of the standard deviation of the cluster sizes to the mean cluster size [79]. The estimated coefficient of variation of 0.47 was calculated from annual attendance at EDs across 170 hospitals in Australia in 2009.

There were limited studies providing estimates of rates of compliance for our primary outcome [82], and no studies undertaken in adult populations. We therefore undertook a retrospective audit of two Australian metropolitan EDs. The estimated rates of appropriate PTA screening for patients presenting in these hospitals (with an initial GCS of 14 or 15) were 0% (95% CI 0% to 14%; n = 24) in one hospital, and 31% (95% CI 24% to 39%; n = 164) for a second (which had an mTBI protocol in place) ([name], [name], unpublished observations). We expected that hospitals without a protocol for mTBI would be more interested in participating in the trial, and therefore calculated our sample size based on a control group rate of 10% (that is, closer to the estimated rate in the hospital with no protocol in place). We wish to detect an absolute increase in the rate of appropriate PTA screening of at least 20%. Our rationale for selecting a difference of 20% is based on considering the size of effect required to justify a resource intensive intervention such as NET, and estimates of the effects of local opinion leaders on professional practice observed across a range of studies [83].

To detect an absolute increase of 20% in the rate of appropriate PTA screening (equivalent to an odds ratio of 3.9, log odds 1.3) (assuming a control group rate of 10%, an ICC of 0.18, coefficient of variation = 0.47, an average of 30 patient participants per ED, and a 5% significance level) with 80% power, we will require 15 EDs per intervention group. A total of 30 EDs will provide 900 patient participants for whom ED staff management will be assessed. For 900 patient participants, the width of the 95% confidence interval for the observed difference in appropriate PTA screening rates between groups will be approximately ±14% (equivalent to a width of ±0.51 on the log odds scale). Allowing for 10% attrition in EDs, we plan to initially recruit 17 EDs per intervention group.

Power is dependent on the selected parameters, but in cluster trials is primarily determined by the chosen ICC and control group rate. Assuming all other parameters are as defined above, a lower control group rate (for example, 5%) will result in greater power (87%), while a higher control group rate (for example, 30%) would result in less power (60%). A smaller ICC (for example, 0.10) would result in greater power (94%), while a larger ICC (for example, 0.30) would result in less power (59%).

Sample size calculations were undertaken using the module *clustersampsi*[84] implemented in the statistical package Stata (StataCorp LP, USA) [85].

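### The ±0.51 given as the 95% confidence interval half-width on the log-odds scale equals one standard error; the half-width is about ±1.0

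*Protocol article*

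**What the plan says.** All the relevant statements are in the Sample size section of the protocol article. The target effect is given on both scales: "To detect an absolute increase of 20% in the rate of appropriate PTA screening (equivalent to an odds ratio of 3.9, log odds 1.3"). The assumptions are listed as "assuming a control group rate of 10%, an ICC of 0.18, coefficient of variation = 0.47, an average of 30 patient participants per ED". With "a 5% significance level) with 80% power, we will require 15 EDs per intervention group", the trial has 30 EDs and 900 patients. The protocol then gives the expected precision: the 95% confidence interval for the difference between groups "will be approximately ±14% (equivalent to a width of ±0.51 on the log odds scale"). The sentence presents the log-odds figure as the same 95% interval on a second scale.

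Under Effectiveness analysis, binary outcomes are to be analysed by generalised estimating equations with a logit link. The models yield odds ratios, risk differences are derived from them as an aid to interpretation, and every estimate is reported with a 95% confidence interval.

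**The concern.** The two half-widths cannot both describe a 95% interval from this design. The same paragraph puts the target at "equivalent to an odds ratio of 3.9, log odds 1.3". A 95% half-width of 0.51 around a log odds ratio near 1.35 would put the estimate more than five standard errors from zero, yet the paragraph claims only 80% power. One of these figures must be on a different footing.

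The log-odds scale is the one on which the primary model estimates the intervention effect. A reader who takes ±0.51 at face value will expect an odds ratio known to within a factor of about 1.7 either way (exp(0.51) = 1.67). The design gives a factor of about 2.7 (exp(1.00) = 2.72). When the observed interval proves about twice as wide as announced on the log scale, it may look as though the trial underperformed.

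**Working it through.** **Inputs, all from the Sample size section.** Control rate p1 = 0.10; intervention rate p2 = 0.30; ICC = 0.18; coefficient of variation of cluster size = 0.47; mean cluster size m = 30; 15 EDs per arm, so 450 patients per arm; 5% significance level (two-sided, per Effectiveness analysis).

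**Step 1. Effect on the log-odds scale.** OR = (0.30/0.70)/(0.10/0.90) = 3.857 and ln(3.857) = 1.350. The stated 3.9 and 1.3 reproduce (1.3499 rounds to 1.3).

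**Step 2. Design effect and effective sample size.** DE = 1 + [(1 + CV²)m − 1] × ICC = 1 + [(1 + 0.2209) × 30 − 1] × 0.18 = 7.413. Effective n per arm = 450/7.413 = 60.7.

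**Step 3. Power, to confirm that these are the plan's inputs.** With 15 EDs per arm, power is 79.4% (z, pooled variance), 81.2% (z, unpooled) or 78.4% (t, 28 df), against 80% stated. The four sensitivity powers in the same section (87%, 60%, 94%, 59%) reproduce on the t basis.

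**Step 4. Risk-difference precision.** SE = √{[p1(1−p1) + p2(1−p2)]/60.7} = √[(0.09 + 0.21)/60.7] = 0.0703. Half-width = 1.96 × 0.0703 = 0.138, or 0.144 with t on 28 df. The stated ±14% reproduces.

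**Step 5. Log-odds precision.** SE = √{[1/(p1(1−p1)) + 1/(p2(1−p2))]/60.7} = √[(1/0.09 + 1/0.21)/60.7] = 0.511. Half-width = 1.96 × 0.511 = 1.00, or 1.05 with t on 28 df. The stated ±0.51 does not reproduce as a half-width; it agrees to two decimals with the standard error.

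**Step 6. Could another derivation give ±0.51?** The 95% half-width on the log-odds scale under other choices is:

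| Variant | Half-width |
|---|---|
| Pooled rate of 20% in both arms | ±0.89 |
| Cluster-size variation omitted (DE = 6.22) | ±0.92 |
| Both arms at 10% | ±1.19 |
| Both arms at 30% | ±0.78 |
| Both arms at 50% (smallest possible variance) | ±0.71 |
| Limits 16% and 44% converted to log odds, control fixed at 10% | ±0.71 |
| Clustering ignored | ±0.37 |

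None gives 0.51. For 0.51 to be correct at 10% v 30% with 900 patients, the standard error would have to be 0.51/1.96 = 0.260. The effective n per arm would be 15.873/0.260² ≈ 234 and the design effect 450/234 ≈ 1.92, so the ICC would be 0.92/35.627 ≈ 0.026 instead of 0.18.

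**Step 7. Consistency with the stated power.** If ±0.51 were the half-width, z = 1.350/0.260 = 5.2 and power would be about 99.9%. With 0.51 as the standard error, z = 1.350/0.51 = 2.65 and power on the log-odds scale is about 75% (z), which is of the order of the stated 80%.

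**Step 8. Interval around the target odds ratio.** With ±0.51: exp(1.350 ± 0.51) = 2.3 to 6.4. With ±1.00: exp(1.350 ± 1.00) = 1.4 to 10.5. With t on 28 df (±1.05): about 1.35 to 11.0.

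**The case against.** The best defence concerns weight, not arithmetic. The figure is a parenthetical restatement that nothing else in the protocol uses. The trial was sized on an absolute increase of 20 percentage points, the precision on that scale (±14%) is right, and risk differences will be reported. The final interval will come from the fitted model with robust variance, so a wrong anticipated width cannot bias the result. All of this stands, and it limits the point to a correction of one stated figure. It does not make the figure right, and odds ratios are the model's direct output, so the log-odds scale is not incidental.

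Three narrower objections also have merit. First, the protocol does not say how 0.51 was obtained, so a missing multiplier of 1.96 is inferred from the numerical match. The finding that ±0.51 is wrong as a 95% half-width does not depend on that inference. Second, the plan's sensitivity powers appear to rest on a t distribution, under which the half-width is ±1.05, so about ±1.0 is the appropriate rounding. Third, the odds ratio of 3.9 and log odds of 1.3 are correct and need no change.

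Reading the word width as the full interval width does not help: the full width would be about 2.0, and the ± sign and the pairing with ±14% mark it as a half-width.

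**Conclusion.** The stated log-odds precision is wrong. On the protocol's own assumptions the 95% half-width is about ±1.0 (1.00 with z, 1.05 with t on 28 df), not ±0.51, so precision on that scale is overstated by a factor of 1.96 (2.05 with t). The error is confined to that figure: the 15 EDs per arm, the power figures and the ±14% all reproduce.

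The conclusion rests on the rates, ICC, cluster size and coefficient of variation in the Sample size section, and on the usual large-sample variance of a log odds ratio inflated by the design effect. It describes an unadjusted comparison of 30 EDs, as the protocol's own calculation does. The width actually observed will also depend on covariate adjustment, the realised ICC and the number of EDs retained.

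**What to change.** In the Sample size section, replace the parenthesis after ±14% with a statement that the 95% half-width is about ±1.0 on the log-odds scale, corresponding to an expected interval of about 1.4 to 10.5 around an odds ratio of 3.9. Alternatively, keep 0.51 and label it as the standard error of the log odds ratio. If the figure is repeated in the statistical analysis plan, which is not shown here, correct it there too.

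The change is one line. It adds no EDs or patients and alters neither the power nor the analysis; the only consequence is that the announced precision on the odds-ratio scale becomes less favourable.

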### Effectiveness analysis

The effectiveness of the intervention on management outcomes, predictors of management outcomes, and patient outcomes will be estimated with marginal modelling using generalised estimating equations. These models will appropriately account for correlation of responses of individuals within EDs. We plan to fit an exchangeable correlation structure where responses from the same ED are assumed to be equally correlated [86]. We will use robust variance estimation which yields valid standard errors even if the within-cluster correlation has been incorrectly specified [87,88]. For binary outcomes, a logit link will be used.

Models will include adjustment for minimisation factors (size (annual presentation rate in 2012), existence of an mTBI protocol, NET or NET-Plus, and rurality) and pre-specified potential confounding variables (Figure 3). The potential confounding variables have been selected through discussion amongst the investigators and from published research. All pre-specified confounders will be included in the models even when no baseline imbalance exists. In addition, for continuous outcomes which are collected at both baseline and follow-up (for example, clinicians’ self-reported cognitions, social and environmental influences in relation to the key behaviours, cognitions about their organisation and team climate) we will include the baseline measure of the outcome in the model. Adjustment for the baseline measure of a continuous outcome yields unbiased estimates of intervention effect in circumstances where there is baseline imbalance, and has the benefit of providing the most powerful analysis [89]. Our primary effectiveness analysis will be the model (as described above) that estimates the intervention effect on the primary outcome, appropriate PTA screening.

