**Figure 3 F3:**
[figure not shown]
**Confounders.** mTBI, mild traumatic brain injury; NET, Neurotrauma Evidence Translation.

Estimates of intervention effect from these models with binary outcomes will yield odds ratios. To aid interpretability, we plan to also provide estimates of risk differences [90]. Estimates of risk differences will be computed from marginal probabilities estimated from the fitted logistic models [91].

Missing data for the clinical practice outcomes are likely to be minimal since eligible patients will be identified and data extracted through chart audit. Missing data could arise if EDs choose to withdraw post-randomisation but prior to data being extracted from clinical records, resulting in empty clusters. Accounting for empty clusters requires strong assumptions to be made about patient characteristics and outcomes based on ED staff or ED characteristics. We will attempt to examine the potential impact of empty clusters on the intervention effects for the clinical practice outcomes using weights to allow for patterns of ‘missingness’ [92]. For continuous outcomes, generalised estimating equations yield unbiased estimates of intervention effect when 1) data are missing completely at random, or 2) when the correlation structure is correctly specified and known covariates that are associated with the missing data mechanism are included in the model (missing at random) [93,94]. For the continuous proxy measures of clinical practice and hypothesised mediators, we plan to identify potential predictors of missing data through modelling (for example, [95]), and include these predictors in the primary analysis model. We will investigate methods to impute missing outcome data collected at baseline (for example, baseline behavioural constructs) [96].

All estimates of intervention effect will be reported with 95% confidence intervals. No adjustment will be made for multiple testing. All tests will be two-sided and carried out at the 5% level of significance. A full statistical analysis plan will be developed and written prior to undertaking any data analysis.

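### The robust variance is called valid without qualification, but with 30–34 EDs and four ED-level covariates the standard uncorrected version, with a z reference, has type I error of about 9–13% rather than 5%

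*Protocol article*

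**What the plan says.** The Effectiveness analysis section of the protocol article specifies marginal models by GEE with a logit link for binary outcomes. On the working correlation: "We plan to fit an exchangeable correlation structure where responses from the same ED are assumed to be equally correlated". On the variance: "We will use robust variance estimation which yields valid standard errors even if the within-cluster correlation has been incorrectly specified". Every model adjusts for four minimisation factors (annual presentations, an existing mTBI protocol, NET or NET-Plus, rurality), all of which are ED characteristics. All pre-specified confounders listed in Figure 3 are added whether or not there is imbalance. This model is the primary effectiveness analysis. The same section sets the test: "All tests will be two-sided and carried out at the 5% level of significance".

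On the number of clusters, the Sample size section says "with 80% power, we will require 15 EDs per intervention group", and then "Allowing for 10% attrition in EDs, we plan to initially recruit 17 EDs per intervention group".

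The section promises a full SAP before any data analysis. It mentions no finite-sample correction to the variance, no t reference and no degrees-of-freedom rule.

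**The concern.** The sandwich variance tolerates a wrong working correlation because it estimates the variance from residuals summed within clusters. That works when there are many clusters. With about 30, the fitted model absorbs part of the between-ED variation, the residuals are too small and the standard error is biased low. Each ED-level covariate makes this worse because it uses up one of the few independent units. A z reference then ignores the uncertainty in the variance estimate itself.

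The primary model has at least six ED-level parameters: intercept, arm and four minimisation factors. If the SAP and the analysis take the validity statement at face value, the primary test will reject a true null well above 5% and the 95% intervals will under-cover. The same rule governs the secondary outcomes and the risk difference derived from the model.

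**Working it through.** **Inputs, all from the Sample size section.** "assuming a control group rate of 10%, an ICC of 0.18, coefficient of variation = 0.47, an average of 30 patient participants per ED"; effect 10% v 30%; 15 EDs per arm (30), 17 per arm recruited (34); two-sided 5%.

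**Step 1: reproduce the sample size.**
- Design effect = 1 + ((CV² + 1)m − 1) × ICC = 1 + ((0.2209 + 1) × 30 − 1) × 0.18 = 7.41.
- Individually randomised n per arm, unpooled variance = (1.96 + 0.84)² × (0.10 × 0.90 + 0.30 × 0.70) / 0.20² = 58.9.
- EDs per arm = 58.9 × 7.41 / 30 = 14.5, so 15. This reproduces the plan. 30 / 0.9 = 33.3, so 34 EDs recruited.

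**Step 2: the reference distribution behind the plan's power figures.** With 450 patients per arm, SE = √(0.30 × 7.41 / 450) = 0.0703 and 0.20 / 0.0703 = 2.845. Base-case power is 81.2% with a normal reference and 78.4% with a noncentral t on 28 df. The four sensitivity powers separate the two:

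| Change | Stated | t, 28 df | Normal |
|---|---|---|---|
| Control rate 5% | 87% | 87.3% | 89.5% |
| Control rate 30% | 60% | 60.2% | 63.2% |
| ICC 0.10 | 94% | 93.8% | 95.2% |
| ICC 0.30 | 59% | 59.0% | 62.0% |

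The stated sensitivities match the t version. The design calculation therefore appears to allow for few clusters, while the analysis text names no such allowance.

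**Step 3: analytic approximation.** Let K be the number of EDs and p the number of ED-level parameters. Suppose the SE shrinks by √((K − p)/K) and the statistic follows t on K − p df. The real error of a test at 1.96 is then the two-sided t tail beyond 1.96 × √((K − p)/K). For K = 30:
- p = 2: 1.96 × 0.966 = 1.894, error 6.9%.
- p = 6: 1.96 × 0.894 = 1.753, error 9.2%.
- p = 10: 1.96 × 0.816 = 1.600, error 12.5%.

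For K = 34 and p = 6 it is 8.6%. This leaves out unequal ED sizes and the low event rate, so simulation should give more.

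**Step 4: simulation under the null.** Beta-binomial outcomes, gamma ED sizes (mean 30, CV 0.47), exchangeable logit GEE, 3,000 trials per scenario (simulation error about ±1 point). Covariate prevalences of 30–50% and a minimum ED size of 5 are assumptions, as the documents do not give them. KC is the Kauermann-Carroll correction.

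| Scenario | Sandwich, z | Sandwich, t(K−p) | KC, t(K−p) |
|---|---|---|---|
| 30 EDs, no covariates, rate 10% | 8.0% | 6.9% | 6.1% |
| 30 EDs, 4 ED-level, rate 10% | 11.6% | 9.8% | 6.0% |
| 34 EDs, 4 ED-level, rate 10% | 10.8% | 9.3% | 6.4% |
| 30 EDs, 4 ED-level, rate 20% | 9.7% | 8.2% | 5.1% |
| 30 EDs, 4 ED-level, rate 30% | 9.6% | 8.1% | 5.2% |
| 30 EDs, 4 ED-level, rate 10%, ICC 0.10 | 11.3% | 10.0% | 6.1% |

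- With covariates and ED size balanced across arms, as minimisation intends, the z column runs from 9.0% to 11.7%. It reaches 14.2% if the rate is 5% without and 25% with a protocol.
- Separately coded runs with four ED-level covariates at the plan's inputs gave 11–13%. Logit-normal EDs gave 12.3%, so this is not an artefact of the beta-binomial model.
- In one such run the mean robust SE was 0.54 against a true SD of 0.68. Then 1.96 × 0.54 / 0.68 = 1.56, which by itself implies an error of 12.0%.
- Scaling the variance by K/(K − 1) lowers the error by only about 0.2–0.7 points.
- A t reference without a variance correction still leaves 7.7–12.5% with four covariates.
- Mancl-DeRouen with z gives 3.6–4.6% with four covariates. With t it is conservative (3.2% at the plan's inputs).

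**Step 5: power under the corrected test.** For 10% v 30%, KC with t and four uninformative covariates, simulated power is about 75% with 30 EDs (75–77% across runs) and about 81% with 34.

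**The case against.** The strongest objection is that the article never says the variance is uncorrected. Kauermann-Carroll and Mancl-DeRouen estimators are themselves robust variances, so the text is compatible with using one. Finite-sample corrections are typical SAP content and a SAP is promised. The match of the power figures to a t on 28 df also suggests authors who were aware of the issue. This stands in part: a reader might infer that the trial has committed itself to a plain sandwich with z, and the documents do not show that. What does not fall away is the statement actually made, which claims valid standard errors without any condition on the number of clusters.

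It can also be said that the validity clause concerns only misspecified correlation. That is its context, but the property is asymptotic in clusters whatever its purpose, and it is offered here as the reason for the choice.

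Three stronger readings are tempting and not supported:
- **A specific, much larger error for NET-Plus outcomes.** The number of NET-Plus EDs is not given, the NET/NET-Plus factor would be constant within that subset, and the primary patient outcome there is an anxiety score rather than a 10% binary event.
- **An error of 15–20%.** Simulation gives 15–18% with eight ED-level covariates and 19.6% with nine, but Figure 3 is not shown and many of its confounders may be at patient or staff level. These figures are illustrative only.
- **A trial that is underpowered once corrected.** That holds only at 30 EDs with uninformative covariates. At the 34 recruited, power is about 81%, and the minimisation factors are expected to be prognostic.

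The remedy is not exact either: KC with t gives 5.1–6.4% in most four-covariate scenarios and 7.4% in the sparsest.

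**Conclusion.** The concern holds as a fault in the stated justification and in what follows if the text is applied as it reads. With the four named ED-level factors and 30–34 EDs, the standard uncorrected sandwich with z has type I error of about 9–13% against a nominal 5%. At the plan's own 10% rate and ICC of 0.18 it is about 11–13%; the lower values come from higher rates or a combination of more EDs and a lower ICC. Intervals are too narrow to match.

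The result rests on assumed covariate prevalences and outcome distributions, and on no correction being applied, which is inferred from none being named. ED-level confounders from Figure 3 would raise it by an amount that cannot be fixed from the documents. A clear effect would survive correction; a borderline primary result could not be relied on at its stated level.

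**What to change.** Qualify the validity statement as a large-number-of-clusters property. Specify, in the SAP and before any analysis, a bias-corrected sandwich variance (for example Kauermann-Carroll, with Mancl-DeRouen as a sensitivity analysis). Base tests and intervals on t with degrees of freedom equal to the number of EDs minus the number of ED-level parameters: 30 − 6 = 24, or 34 − 6 = 28, with the four minimisation factors alone. Apply this to the primary model, to the confidence interval of its risk difference and to the other GEEs. State how many Figure 3 confounders are at ED level, because each costs a degree of freedom.

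Report planned power under this test: about 75% with 30 EDs and about 81% with 34, for 10% v 30% with four uninformative covariates. The cost is a few lines of SAP text and a standard software option. The downside is wider intervals and slightly lower stated power.
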